## Abstract

**Background:**

Shared decision-making is a process that involves collaborative discussions between a patient and a care team to ensure informed healthcare decisions. This process becomes more complex when the older person’s decision-making capacities are affected. In these situations, surrogate decision-making processes are used to define a person-centered care plan. Despite these processes, the implementation of the care plan defined in the best interest of the patient may nevertheless be rejected by the patient, particularly in cases of neurocognitive disorders or delirium. This concept of opposition and/or refusal is frequently used in research. This is not yet well understood in the medical literature, and there is a lack of consensus on its definition. We, therefore, explored this concept by defining opposition to diagnostic or therapeutic proposals.

**Method:**

Our pilot study protocol is based on a mixed methodology (epidemiological and qualitative research) to quantify this phenomenon, validate the proposed definition, and explore its core elements. Opposition and refusal of care will be quantified, and semi-structured interviews will be conducted with patients, their relatives, and referring carers. Multidisciplinary meetings that will be associated with these situations will also be observed and analyzed. Methodological approaches that can be used to explore opposition and refusal of care in a scientific, reproducible framework are presented. This methodology considers the specificities of the geriatric, polypathological population with neurocognitive disorders.

**Discussion:**

Opposition and refusal of care are key concepts in clinical research on ethics, particularly in the geriatric field. These concepts are frequently mentioned in studies involving older patients but have not been specifically defined or studied. This study would undoubtedly lead to greater awareness among professional caregivers and relatives of the significance of such opposition, and more respectful interactions in these complex hospitalization cases.

**Trial registration:**

ClinicalTrial.gov, NCT03373838. Registered on 14 December 2017.

## Background

Projections of population aging show that the proportion of people over 60 years of age in developed countries will increase from 20 to 30% between 2005 and 2050 [1]. Population aging is explained by the age pyramid but also by the increase in life expectancy. A particular effect associated with population aging is the increase in the use of health systems by people with multiple chronic diseases [2]. As we age, the management of polypathology becomes more complex; frailty gradually sets in, and various functional, psychological, social, and ethical issues need to be taken into account [3]. The number of older dependent people is also increasing with population aging [4]. Concomitantly, hospital use by older people with polypathology and dependence is high. Indeed, nearly 40% of patients over 75 years of age are hospitalized following a visit to the emergency department [5]. During these hospitalizations, many health-related decisions are made.

Health decisions must be based on the free and informed consent of the person involved. This principle, although already in use, was first universally recognized in the Nuremberg Code in 1947. It was later developed and refined, concerning both biomedical research and the practice of medicine. In this respect, various laws refer to patients’ freedom of decision, such as Article L. 1111-4 of the *French Public Health Code*: *No medical act or treatment may be performed without the free and informed consent of the person and such consent may be withdrawn at any time* [6, 7]*.* Thus, during hospitalization, each medical procedure is subject to the patient’s consent, if he/she can consent [8, 9]. When the person is no longer able to express his or her will, that is to say, based on the Mental Capacity Act (UK)—Section 3, that the person is no longer able: (a) to understand the information relevant to the decision, (b) to retain that information, (c) to use or weigh that information as part of the process of making the decision, or (d) to communicate his decision (whether by talking, using sign language or any other means), then surrogate decision-making should be made.

This surrogate decision-making includes substituted (trusted person) or delayed consent (advance directives) in a deliberative process to choose the most appropriate care option for the incapable person. Decision support frameworks are then based on the person-centered care approach to ensure the primacy of individuals’ health and life goals in their care planning and their actual care [10].

Despite changes in decision-making capacities associated with aging (see systematic review on this subject [11]), the older patient will make his/her choice according to rational and irrational information, and the stability of this choice overtime is expected [12]. Several tools have been developed [8, 13] to facilitate this assessment by health professionals, particularly in cases where the ability to consent is uncertain. Indeed, older patients are more likely to present alterations in decision-making processes due to neurocognitive disorders (even in mild stages) that create barriers to enlightened choices [14–19]. This is particularly the case during delirium [20].

Yet, routine care situations and low-risk procedures are rarely presented as choices, even though the patient has the right to refuse them [21]. Existing clinical tools assessing the ability to consent (e.g., [8, 19]) are therefore not used in this context. Patient’s opposition in situations that are not perceived by health professionals as open-ended proposals may lead to conflictual situations, in particular, if these situations are seen, by professionals, to be respectful of patient-centered care approach (e.g., antibiotics administration and blood test to treat sepsis and being able to discharge the patient to home). When a patient’s choice goes against medical strategies, the capacity to consent is often contested, as health professionals are reluctant to accept the risks involved [22]. Indeed, this situation opposes two contradictory obligations: on the one hand, the need to respect the person’s right to make a decision, according to the principle of autonomy, and on the other hand, the need to protect individuals, according to the principle of beneficence [23]. This leads to the need to reconsider the therapeutic objectives or the approach implemented and/or to agree collegially to override this opposition in the name of the patient’s best interest. To do this, it is necessary to ensure that the patient’s will and life project are understood, as much as possible, and to combine the skills of professionals to propose a care project adapted to the situation and centered on the person [24]. Nevertheless, despite these elements guaranteeing ethical respect for the approach decided by derogation, this may still lead carers to use procedures for which the patient is opposed.

However, even though the question of oppositional behaviors has been at the heart of many conceptual works in the field of geronto-psychiatry for more than 30 years, its study in clinical situations, and in particular during short hospital stays, remains rare. Indeed, conceptual approaches have used the prism of person-centered care to address the limitations of the care plan. In acute care, older patients may behave in opposition to medical strategies, even though the objective deployed corresponds to the patient’s previous personalized care plan. The technical nature of the treatment may lead the patient to oppose its implementation, particularly in cases of neurocognitive disorders. As such, the question of patients’ opposition to diagnostic or therapeutic proposals is a recurring issue faced by medical and paramedical teams. How can we explore the meaning of this opposition, when, paradoxically, it does not seem nameable, at first glance, by the patient? It is essential for carers and doctors, but also for relatives, who are often at the forefront of delegated decision-making processes [25], to obtain explanatory elements on this question to better position themselves and find the right balance between patients’ right to autonomy and the need to intervene to preserve his/her health.

## Hypotheses

The hospitalization of polypathological seniors represents a break in their life course. The technicity of medical care is generally engaged in a systematic way and often contributes to acute decompensation [26]. However, even though some medical interventions (e.g., insertion of a venous catheter for hydration or antibiotic therapy, additional medications, bandaging, biological check-ups) may seem, in the best interest of the patient, acceptable and necessary according to caregivers, and as such, compatible with internationally recognized legal and moral safeguards, their implementation may lead to vehement or even violent opposition if they exceed patient’s tolerance and dependence threshold [27]. Another hypothesis is that patients may not feel that their best interest is considered in recommended procedures. These patients may thus oppose diagnostic or therapeutic procedures to demonstrate their need or capacity to control their situation. Finally, the question of anosognosia and neurocognitive disorders raises the question of the meaning of treatment. Memory disorders may alter patients’ recollection of acute events once symptoms have been controlled, particularly if these events generated episodes of delirium.

A quantitative study seems necessary to quantify and better understand the parameters associated with situations involving opposition to diagnostic and therapeutic procedures. Although these events are often mentioned in medical literature, they are not documented or compiled in hospital records. Epidemiological studies must be associated with qualitative and comprehensive analyses of events to ensure an in-depth understanding of the opposition expressed by older patients. Is this opposition linked to a distorted and negative representation by patients of the proposed diagnostic or therapeutic procedure? In older people with a certain degree of delirium and/or cognitive deterioration, treatment may be perceived as a threat, intrusion, coercion, obstruction, violence, or even aggression. It is therefore conceivable that some intrusive procedures may be refused. Is this opposition an expression of a desire to control one’s own life until death? Is it not the ultimate expression of the existence of oneself, the expression of an ability to decide for and by oneself, in a world characterized by several constraints and dependence for all acts of daily life? Is this opposition expressing a feeling of indignity experienced in a societal context, or a reaction to ageist tendencies [28, 29] that can generate a sense of social uselessness among the older population? The qualitative component of the present study also contributes to the exploration of interactions between doctors, carers, and relatives confronted with patient opposition; the functioning of collegial meetings and decision-making methods are also addressed to better understand some consequences of the dilemma that arises in cases of opposition to diagnostic or treatment in older patients.

In order to answer these questions and verify the aforementioned hypotheses, it is necessary, in view of the specificities of opposition to medical care and target population (older people, including persons with neurocognitive disorders), to carry out a pilot study beforehand, with the following specific objectives:
To verify the applicability of the proposed definition of opposition to medical care and its reproducibilityIdentify the proportion of patients expressing opposition to medical care according to the proposed definitionIdentify the key elements to be included in the qualitative interview, based on a preliminary interview grid.

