### Definition of opposition

To date, there is no scientific consensual definition of opposition to treatment or diagnostic procedures. In the OPTAH study, we will define opposition to treatment or diagnostic procedures as follows:
The repeated (at least twice in a row, with at least two separate interlocutors) and explicit (verbal or physical) expression of an opposition. Oppositions expressed during the usual meetings between doctors and patients are not included in the analysis if they are part of a free and informed choice, even if they may concern a decision (acceptance or refusal) of a therapeutic proposal. Opposition behaviors concern either of the following:
Medication intakeInvasive diagnostic or therapeutic procedures (biological check-up, imaging, endoscopy, biopsy, etc.)Removal by the patient of a venous, nasogastric, or urinary catheterIn the absence of consent or acceptance by the patient of similar treatments during the reporting period

It should be noted that we will not include in this definition non-medical care (meals, shower, massage, physiotherapy) if it does not have medical consequences, to avoid confounding factors and information gathering issues. Opposition to non-medical care deserves separate research studies. Thus, patients who oppose treatments or diagnostic procedures will be included in the study even though they otherwise accept non-medical care. Symmetrically, patients who do not oppose treatments and diagnostic examinations but who refuse care (meals, shower, massage, etc.) will not be included in the study unless their refusal (e.g., to drink) may lead to the development of a medical pathology (e.g., functional kidney failure due to dehydration) or medical consequences, for which they refuse medical investigation or treatment.

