#### Epidemiological component

When patients will present opposition to a diagnostic or therapeutic procedure, they will be included in the epidemiological component of this study by the attending physician. The physician will complete a data collection form to initiate the patient’s participation in the study. This form covers the patient’s general demographic and medico-social data. It focuses on the information related to the opposition that had occurred (drugs, procedures) and on the circumstances of the opposition (e.g., organ failure, sepsis, delirium). This survey will also be completed at discharge, to describe the outcomes resulting from this opposition (respect or not for the patient’s position, healthcare strategy, mortality).

The data collected are detailed below, in the “Data analysis” section.

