#### Epidemiological component

The medical and medico-social data used for the quantitative component will be compiled in a standard electronic form. The data will be collected during the consultation of the patients’ usual medical records including H24 daily notes from medical, nurses, and auxiliary nurses.

To characterize the population under study, the following data will be used:
Demographic characteristics of patients (age, gender)Medical data of patients that are generally collected at the time of their admission (history, usual medications, nutritional, cognitive, motor, thymic status)Medico-social data relevant to the standardized geriatric assessment usually carried out in the service (capacity to perform activities of daily living, instrumental activities of daily living, place, way of life, presence of family and relatives, home-support workers)

To define oppositional behaviors, the following data will be collected:
Circumstances of the opposition (who notices it, when, who reports it in the care record, recurrence of the event)Patient’s oppositional attitude (oral argumentation, physical opposition, catheter removal, type, duration)The target of opposition (single clinical element or overall attitude of catheter withdrawal and refusal of the procedure, taking medication, etc.), medication (molecule, route of administration), and/or material (venous, nasogastric, or urinary catheter) that triggered patients’ oppositionMedical circumstances (organ failure, sepsis, delirium, etc.) surrounding the refusal of diagnostic or therapeutic procedures

To better understand the consequences of the opposition behavior, the following data will be collected:
Medical decisions about the diagnosis or therapeutic strategies (continuation despite patient’s opposition or acceptance of patient’s opposition and change of medical orientation)The organization of the collegial meeting and the reasons involvedPatients’ outcomes following the opposition behavior (discharge, transfer to another unit, death)

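### The pilot aims to verify that its definition of opposition is reproducible and to validate it, but the article describes only one application of the definition and no agreement analysis

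*Protocol article*

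**What the plan says.** - **Aim.** The specific objectives at the end of the Hypotheses section begin with "To verify the applicability of the proposed definition of opposition to medical care and its" reproducibility. The Method paragraph of the abstract says the mixed methodology will "quantify this phenomenon, validate the proposed definition, and explore its core elements". The later Study objectives section names only the frequency and the meaning of opposition, and neither of these two aims.
- **Who applies the definition.** Under Experimental planning, Epidemiological component, patients in opposition are identified and "they will be included in the epidemiological component of this study by the attending physician". Then "The physician will complete a data collection form to initiate the patient’s participation in the study". The form is completed again at discharge, but to record outcomes.
- **Who enters.** The Inclusion criteria require opposition as the article defines it.
- **What the definition asks.** It requires repetition, "at least twice in a row, with at least two separate interlocutors", and it sets aside oppositions voiced in ordinary consultations, which "are not included in the analysis if they are part of a free and informed choice".
- **Analysis.** Statistical analysis of epidemiological data gives descriptive summaries and chi-square or Student tests at the 0.05 level. It names no measure of agreement or classification error.

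**The concern.** Reproducibility of a definition means that two people applying it to the same events reach the same answer. To estimate it, at least some events must be rated twice, and the rated set must include events that one rater would turn away. The article describes neither.

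The question is a real one here. Whether a refusal reflects an informed choice is a judgement, and two physicians may well differ on it in a patient with delirium or cognitive impairment. The second specific objective, the proportion of patients in opposition, rests on the same classification. If the aim stays as worded and no agreement data are gathered, the report cannot answer that half of its first objective, and a later study may rely on a definition whose reproducibility was announced but never measured.

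**Working it through.** The article gives no sample size, kappa or precision for this aim, so there is no figure to reproduce. The check has three parts.

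**1. Could anything described serve as a second rating?**

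- The two interlocutors in Definition of opposition are people to whom the patient repeats the refusal. They are a clause of the definition, not two raters.
- The form records "Circumstances of the opposition (who notices it, when, who reports it in the care record, recurrence of the event". This describes the event and does not re-classify it.
- The 60-patient reference set holds medical and socio-demographic data. No rating against the definition is described.
- The two researchers in Qualitative methodology analyse interview transcripts for themes.
- The roughly ten interview situations are drawn from patients already classed as in opposition.

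None of these is a second application of the definition to an event.

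**2. Would re-reading only the included situations be enough?**

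Cross-classify two raters: *a* both yes, *b* first yes and second no, *c* first no and second yes, *d* both no, *n* the total.

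- Observed agreement: po = (a + d)/n
- Chance agreement: pe = [(a + b)(a + c) + (c + d)(b + d)]/n²
- kappa = (po − pe)/(1 − pe)

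Study status reports 33 situations after 20 months. If only these are read, c = d = 0 and both po and pe equal a/n.

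| Second reader disagrees on | po | pe | kappa |
|---|---|---|---|
| 0 of 33 | 1.000 | 1.000 | undefined (0/0) |
| 3 of 33 | 0.909 | 0.909 | 0 |
| 6 of 33 | 0.818 | 0.818 | 0 |
| 10 of 33 | 0.697 | 0.697 | 0 |

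Such a reading would give the share of inclusions that a second reader confirms, but nothing on missed events. To show how much depends on the refusals turned away, keep the included row at 30 agreed and 3 not, and assume 33 refusals that the first rater judged not to qualify. Then n = 66, pe = 0.5 and po = (30 + d)/66.

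| Of the 33 turned away, second rater would include (c) | po | kappa | Second rater's positives captured by the first, 30/(30 + c) |
|---|---|---|---|
| 0 | 0.955 | 0.91 | 100% |
| 3 | 0.909 | 0.82 | 91% |
| 10 | 0.803 | 0.61 | 75% |
| 20 | 0.652 | 0.30 | 60% |

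The same included row is compatible with a kappa anywhere from 0.91 to 0.30.

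**3. What would a modest double rating give?**

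Assume 60 extracts (about the 33 included plus some 30 near-misses), balanced classes (pe = 0.5) and kappa 0.7. Then po = 0.5 + 0.7 × 0.5 = 0.85.

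SE = √[po(1 − po)/(n(1 − pe)²)] = √[0.85 × 0.15/(60 × 0.25)] = √0.0085 = 0.092, and 1.96 × 0.092 ≈ 0.18.

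With balanced classes this formula reduces to √[(1 − kappa²)/n]:

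- kappa 0.6: 1.96 × √(0.64/60) ≈ 0.20
- kappa 0.8: 1.96 × √(0.36/60) ≈ 0.15

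The large-sample variance for two raters under a common-correlation model agrees: 66 extracts give ±0.19 at kappa 0.6 and ±0.15 at kappa 0.8.

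**The case against.** The strongest reply is that silence is not exclusion. The article names one classifier but nowhere rules out a second rating, and it does not say that refusals falling short go unrecorded. It plans a complete count of opposition situations and draws on round-the-clock notes from doctors, nurses and auxiliary nurses, so near-misses may be retrievable. The full protocol is not shown, nor are the inclusion flow diagram and the planning figure, and an agreement statistic could sit in an analysis plan. This stands as a limit. A reader might infer that each event is definitely rated only once, that near-misses are discarded, and that agreement can never be calculated. The text does not support any of those. It supports only that no such step is described.

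The second reply is that validation in a mixed-methods pilot need not mean kappa or error rates. Accounts from patient, relative, carer and general practitioner are cross-referenced, collegial meetings are observed, and a multidisciplinary team discusses the analysis. This also stands in part. A reader might conclude that the whole first objective fails, but applicability can be partly described from recruitment and form completion, and interviews can inform content validity. Reproducibility gains nothing from these sources.

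Third, the article calls its results exploratory and acknowledges limitations, so the harm to later studies is a risk, not a certainty. That is fair, but it does not supply the missing data.

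**Conclusion.** The concern holds for reproducibility and for quantitative validation. On the design as described, the pilot yields no data on inter-rater agreement or on missed and wrongly included events, so it cannot answer that half of its first objective. This is more than an omitted analysis detail, because no later choice of statistic can replace a second rating that was never made. It does not extend to applicability or content validity, and it is repairable.

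The conclusion rests on the article alone and would change if the full protocol contains a second rating and a record of refusals judged not to qualify. The 33 situations come from the document. The 33 discarded refusals, the kappa values and the balanced mix are assumptions used for illustration.

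**What to change.** **Simplest change.** In the abstract and in the first specific objective, restrict the aim to applicability or feasibility and a description of how the definition was used. Drop reproducibility, and drop validation in any quantitative sense. This costs only the rewording.

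**To keep the aim.** Have two physicians already on the research team, blinded to each other and to the inclusion decision, apply the definition to de-identified extracts of the round-the-clock notes. The extracts should cover the included situations plus near-miss refusals (for example a single refusal, or one judged an informed choice) from patients who do not object to use of their data. Report percent agreement and kappa with 95% confidence intervals, and the clause behind each disagreement.

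**Cost and limits.** This takes reading time and the retrieval of near-misses. Retrieval may be harder than it looks, since the Hypotheses section says these events are not compiled in hospital records. Near-miss patients are not study participants, so any information or approval step for their data must be checked. The result would measure agreement between chart readers in an enriched sample, not bedside agreement at the ward's own prevalence, and should be reported as such.
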